### Recommended clinical practice

Recommendations for antibiotic prescribing are derived from several German high-quality, evidence-based clinical guidelines, most of which were developed by the German College of General Practitioners and Family Physicians (DEGAM) [2, 15]. All guidelines used are systematically developed, evidence- and/or consensus-based and conform with the quality standards for guidelines in Germany [16]. In short, they recommend restrained prescription of antibiotics, particularly in healthy patients with acute non-complicated symptoms. If antibiotics are used, recommended ones should be preferred instead of broad-spectrum antibiotics, like quinolones, for example.

### Primary and secondary outcome measures

The primary as well as the secondary outcomes of the claims data based evaluation are defined and operationalized based on previous research in Germany [17]. Pseudonymized claims data (§§ 295, 300 SGB V) are used to construct different European Surveillance of Antimicrobial Consumption Network (ESAC-Net) indicators [18, 19] measuring the primary and secondary outcomes.

The primary outcome refers to the following index indicator, based on different single ESAC-Net indicators:Percentage of patients with acute non-complicated infections who are treated with antibiotics.

Secondary outcomes refer to the following (ESAC-Net) indicators:2.The use of antibiotics in ambulatory care in defined daily dose (DDD) per 1000 residents (respectively insured persons) per day and region3.Percentage of DDD of broad-spectrum quinolones of all used antibiotics4.Percentage of DDD of broad-spectrum cephalosporins (3rd and 4th generation) of all used antibiotics5.Percentage of patients (18–75 years) with acute bronchitis, patients (> 18 years) with sinusitis, patients (> 2 years) with otitis media and patients (> 1 year) with upper respiratory tract infections/tonsillitis with a prescription of (a) recommended antibiotics, if necessary at all, and (b) less broad-spectrum antibiotics like quinolones6.Percentage of women (> 18 years) with a diagnosis of non-complicated cystitis and a prescription of (a) antibiotics, (b) recommended antibiotics and (c) less broad-spectrum antibiotics like quinolones7.Percentage of patients (18–65 years) with community-acquired pneumonia and a prescription of (a) antibiotics, (b) recommended antibiotics, (c) less broad-spectrum antibiotics like quinolones (> 16 years) and (d) less broad-spectrum antibiotics like cephalosporins or macrolides (> 16 years)8.Percentage of patients with acute non-complicated infections who use medical emergency service9.Percentage of patients with community-acquired pneumonia and hospitalisation

The process evaluation will use a mix of measures to assess the fidelity of the implementation programs, the potential working mechanisms and the impact of health system-related factors on outcomes. The impact of participation in a practice network on implementation of new ideas and practices regarding antibiotic prescribing is of particular interest. Various social mechanisms influence the spread of new attitudes and behaviours, as well as the motivation to change the behaviour [10]. In the exploration, some emphasis will be put on the potential impact of the networks in which the physicians are embedded. Therefore, tailored questions for interviews and surveys are phrased, which cover (a) the uptake and perceived impact of intervention components by participants with a focus on handling patients with acute non-complicated infections, (b) the perceived impact of contextual factors, particularly those related to practice networks, and (c) perceptions of patients’ expectations regarding antibiotic prescribing. The construction of the survey is based on Ajzen’s [20] theory of planned behaviour. The survey items are conform with this theoretical framework of Ajzen [20] and are used to gain specific information about the impact of (a) each intervention component received, (b) contextual factors including structural conditions and organisation of patient care, legal terms and conditions (e.g. legal quality requirements, reimbursement of patient care by statutory health insurance) and participation in a practice network, and (c) perceptions of patients expectation regarding antibiotic prescribing on the behaviour of participating physicians and medical assistants. Items are scored on a 5-point Likert scale ranging from 1 (strongly disagree) to 5 (strongly agree). Interviews will add in-depth understanding of mechanism of action, particularly those related to practice networks, and explore uptake and possible adaption to daily practice of intervention components in more detail. Both surveys and semi-structured interviews include written questions concerning socio-demographic aspects like age, gender, years of working experience and characteristics of the working environment.

Focus group interviews will aim to discuss barriers in implementation of intervention components and to develop possibilities to overcome these barriers.

Patient survey will be used to gain feedback from patients concerning their knowledge and views on antibiotics and antibiotic prescribing, as well as their perception of different intervention components targeting patients. Therefore, a questionnaire will be used covering reason for consultation (complaints/illness), whether antibiotics are expected, requested and received (yes/no questions), as well as (with 4-point Likert scale) patient education and shared decision making on antibiotic prescribing, views on delayed antibiotic prescription, perceived study components, the role of non-physician health professionals of the practice team, general view on antibiotic prescribing in and general satisfaction with the practice. In addition, age, sex, nationality and education are recorded. The questionnaire used in the patient survey is based on published research [21, 22].

### Data collection and data management

#### Outcome evaluation

Primary and secondary outcomes, as well as patient characteristics, will be extracted from administrative data at the health insurers involved, so called claims data. This will be done each quarter year. These data provide the basis for the outcome evaluation and the written feedback for participating practices.

Patient characteristics documented from the administrative data include age, sex, years in insurance, insurance status (principal, family or retired member), patient participation in disease management programs (diabetes, breast cancer, asthma, coronary heart disease, COPD, chronic heart failure) and other additional care programs. In addition, prescribing physician identification, medical discipline and physician participation in disease management programs are recorded.

#### Process evaluation

Written, paper-based questionnaires will be mailed to participating physicians in study arms A, B and C, and in study arm B also to medical assistants. This will be done three times following their quality circle meetings by the study central office. Reminders will be sent out after 2 weeks to increase the response rate. The filled in questionnaire will be sent to the Department of General Practice and Health Services Research, University Hospital Heidelberg. Hence, the survey is pseudonymized, no identification of the participants’ identity will be possible.

The questionnaire will be pilot tested with a sample of four physicians, who are associated with the Department of General Practice and Health Services Research, University Hospital Heidelberg and two non-physician health professionals of the practice team.

Face-to-face and telephone interviews with a sample of 40 physicians and medical assistants as well as an additional sample of 10 stakeholders will be done by researchers. Each interview will take between 30 to 45 min and is conducted using a semi-structured interview guide. The interviews will be audio-recorded, transcribed verbatim and stored on a secured server of the University Hospital Heidelberg. Transcripts will be pseudonymized.

Focus group interviews with one representative of each practice network will be done every 3 months.

#### Patient survey

Sixty AOK-insured patients per participating practice in Bavaria in intervention arm B, who visit the practice with at least one of the relevant index diseases, will be invited to complete a written questionnaire after the consultation. The questionnaire is filled in anonymously by each patient and is collected in a sealed box in each practice. A time slot of maximum 3 months is defined for conducting the survey. Afterwards, the sealed box containing the questionnaires is sent back to the aQua-Institute for data analysis.

A pilot study including telephone interviews with patients will be conducted in advance to ensure that the questions are comprehensible from the patients’ point of view.

### Data analysis

#### Outcome evaluation

The primary objective of this study is to examine the change of the antibiotic prescription rate in targeted patients within three intervention arms and the comparison between the three intervention arms. The confirmatory analysis of the primary endpoint will be conducted on the basis of the Intention-To-Treat (ITT) population where all patients will be included in the analysis and assigned to the group they were randomised to.

To account for multiple testing and to assure a global significance level of 5%, a multiple test procedure for hierarchically ordered hypotheses will be applied. In the first stage, differences regarding the primary endpoint (prescription of antibiotics) before and after the intervention in intervention groups B and C are tested. To assure a significance level of 5% within the first level, the hypotheses for the pre- and post comparison will be tested at a local significance level of 5/2%. The second step includes the pre-and post comparison in intervention group A. The significance level of the rejected hypotheses from step one is taken (2.5% if only one hypothesis can be rejected, 5% if both hypotheses can be rejected). If significance is reached in intervention groups A and B, differences between groups A and B will be tested at a local significance level of 5/2%. Similarly, difference between groups A and C will be only tested if significance is reached for groups A and C in the steps 1 and 2. If the hypotheses in step 1 or 2 cannot be rejected, the group comparison will not be tested primarily.

In all stages described above, a logistic mixed effects model will be applied to assess the respective hypotheses regarding the primary endpoint. In the first and second stage, the time (before/after the intervention) is included as fixed effect. A random intercept will be included for patients and for practices. For the comparisons in the third stage, the intervention group will be included as fixed effect additionally. Furthermore, age and gender will be included as covariates. Finally, sensitivity analyses will be conducted using different populations (per protocol population where patients with major protocol violations are excluded and appropriate subgroups). Since all these analyses are based on claims data, missing values cannot be tracked.

Descriptive methods will be used for the analysis of the secondary outcomes, including the calculation of appropriate summary measures of the empirical distribution (mean, standard deviation, median, IQR, minimum and maximum for continuous variables and frequency in percentages for categorical variables). In addition, similar mixed models as described for the primary endpoint will be used. All calculated *p* values regarding secondary outcomes will have descriptive character only.

Furthermore, differences between the intervention groups and an untreated comparison group will be tested. The comparison group consists of claims data of patients insured by AOK health insurance in non-participating practices in Bavaria and North Rhine-Westphalia. Therefore, propensity score matching will be used to generate 14 virtual clusters of non-participating practices.

A detailed statistical analysis plan is written prior to the final analysis. SAS (SAS Institute Inc., Cary, NC, USA), version 9.4 or higher, is used to carry out the analyses.

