### Sample size calculation

The sample size calculation is based on the expectation to find an absolute reduction of the antibiotic prescription rate in targeted patients from 61 to 50% in intervention group A and from 61 to 45% in groups B and C. Thus, the effect is expected to be 5% higher in the enriched intervention groups B and C compared to intervention group A.

To control the overall type I error rate at 0.05 (two-sided), a hierarchical 3-step testing procedure will be applied. In the first step, the hypotheses of no difference between the pre- and post prescription rate in group B and C will be tested. If at least one of these hypotheses can be rejected, the hypothesis of no difference in the pre- and post rate in group A will be tested. If, additionally, this hypothesis can be rejected, the hypotheses of no difference between the post rates of groups A and B as well as groups B and C will be tested. The sample size is calculated based on chi-squared tests assuring a (global) power of 80% for the rejection of all the above described, hierarchically ordered hypotheses. Furthermore, to take the clustered structure into account, an intra-cluster correlation coefficient (ICC) for patients in practices of 0.05 and of 0.7 for cases clustered in patients is assumed. Together with the above described expected pre- and post prescription rates in the three groups, this results in a sample size of 23,933 patients in group A, 11,967 patients in group B and 11,967 patients in group C. With an average practice size of 80 patients per quarter this leads to 75 practices in group A, 38 practices in group B and 38 practices in group C.

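### Stage three keeps A-B and A-C at a fixed 2.5% each even when the full 5% is available; a Holm step would add about 7 to 10 points of power to reject both, within the 5% limit

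*Protocol article*

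**What the plan says.** The Outcome evaluation section of the Protocol article sets out a three-stage hierarchy for the primary endpoint.

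- **Stage one** (pre-post change in B and in C): "the hypotheses for the pre- and post comparison will be tested at a local significance level of 5/2" per cent.
- **Stage two** (pre-post change in A): the level carried over from stage one, "2.5% if only one hypothesis can be rejected, 5% if both hypotheses can be rejected".
- **Stage three, A-B:** if A and B were significant, "differences between groups A and B will be tested at a local significance level of 5/2" per cent.
- **Stage three, A-C:** "Similarly, difference between groups A and C will be only tested if significance is reached for groups A and C in the steps 1 and" (the quotation breaks off just before the second stage is named). No separate level is printed; the word that opens the sentence implies the same 2.5%.

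Nothing is said about reusing the level of a third-stage hypothesis that has been rejected.

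The Sample size calculation section describes the same hierarchy: "To control the overall type I error rate at 0.05 (two-sided), a hierarchical 3-step testing procedure will be applied". It defines power as "assuring a (global) power of 80% for the rejection of all the above described, hierarchically ordered hypotheses". It lists the third-stage hypotheses differently, however: "the hypotheses of no difference between the post rates of groups A and B as well as groups B and C will be tested".

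**The concern.** The plan already carries level forward from stage one to stage two, so it accepts the principle. It does not apply the principle inside stage three. When B, C and A have all been rejected, 5% is available there and is cut into two fixed halves. Once one contrast is rejected at 2.5%, that 2.5% is free, and the other contrast could be tested at 5% without breaching the overall limit.

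Stage three answers whether either enriched programme beats the standard set, and the comparison between arms is part of the stated primary objective. Global power is defined as rejecting every hypothesis, and stages one and two are almost certain to succeed under the planning assumptions. Stage three therefore decides whether the target is met.

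**Working it through.** **Inputs, all from the Sample size calculation section unless noted.** Rates "from 61 to 50% in intervention group A and from 61 to 45% in groups B and C"; ICC 0.05 for patients in practices and 0.7 for cases in patients; 80 patients per practice; sizes 23,933 (A), 11,967 (B) and 11,967 (C). The 2.5% third-stage level is from the Outcome evaluation section. The pairs used here are A-B and A-C.

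**1. Reproduce the stated sample size.** Two-proportion (chi-squared) formula, 50% against 45%, two-sided 2.5%, allocation A:B = 2:1 (k = 0.5), power 80% for one comparison:

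- Pooled rate: (0.50 + 0.5 × 0.45)/1.5 = 0.4833
- Null term: 2.2414 × √(0.4833 × 0.5167 × 3) = 1.9400
- Alternative term: 0.8416 × √(0.25 + 0.2475/0.5) = 0.7264
- n in A, unclustered: (1.9400 + 0.7264)²/0.05² = 2,844.0
- Design effect: (1 + 79 × 0.05) × (1 + 0.7) = 4.95 × 1.7 = 8.415. The factor 1.7 assumes two cases per patient.
- 2,844.0 × 8.415 = 23,932.4, rounded up to 23,933; half is 11,966.2, rounded up to 11,967.

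This matches the protocol exactly, which supports the two-cases assumption. The effective sizes are about 2,844 (A) and 1,422 (B and C).

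**2. Stages one and two.** At this size, with half the sample before and half after, power is 99.994% for B or C at 2.5% and 99.996% for A at 5%. They do not affect the result.

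**3. Power to reject both contrasts.** A-B and A-C share arm A, so their test statistics are correlated: ρ = (0.25/2)/(0.25/2 + 0.2475) = 0.336. Each statistic has mean 2.2414 + 0.8416 = 3.083. Let Φ₂ be the bivariate normal distribution function.

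- Fixed 2.5% each: Φ₂(0.8416, 0.8416; ρ) = 67.0%
- One at 2.5%, the other at 5% (critical value 1.960): Φ₂(1.1231, 0.8416; ρ) = 71.9%
- Holm rejects both when both p-values are below 5% and the smaller is below 2.5%: 2 × 71.86% − 66.96% = 76.8%

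Gain: 9.8 points.

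**4. Taking the stated 80% at face value.** If the fixed-split probability of rejecting both is set to 80.0%, Holm gives 87.2%, a gain of 7.2 points. The gain runs from 6.9 to 7.7 points as the correlation goes from 0.5 to 0.

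**5. In patients.** With the same design effect, 80% for both contrasts needs about 29,870 in A with fixed tests and about 25,480 with Holm, roughly 15% fewer (25,480/29,870 = 0.853).

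**6. Family-wise error.** The full procedure was simulated with 2 million runs per pattern. Holm was used only when B, C and A were all rejected.

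| True nulls | Fixed | Holm |
|---|---|---|
| A-B and A-C | 4.8% | 4.8% |
| A-B only, very large A-C effect | 2.5% | 5.0% |
| C pre-post and A-B | 5.0% | 5.0% |
| A pre-post | 5.0% | 5.0% |
| All | 4.9% | 4.9% |

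Holm never goes above 5% beyond simulation error. The one marked change, from 2.5% to 5.0%, uses level that the fixed split leaves idle.

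**The case against.** **The plan is not wrong.** A pre-specified Bonferroni split inside a gatekeeping hierarchy is legitimate. A reader might infer from this point that the type I error is miscontrolled. The documents do not support that: the fixed procedure holds 5% in every pattern above. This stands, and it limits the point to efficiency.

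**The analysis plan could refine the step.** A detailed statistical analysis plan is promised before the final analysis and is not shown. But the 2.5% level is fixed in the protocol article's own text, so it is a choice that can be commented on.

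**The change is not wholly free.** Fixed 2.5% tests pair with plain 97.5% confidence intervals, and Holm has no equally simple counterpart. That stands as a small cost.

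**Holm does not restore the stated power.** A reader might take 77% as good enough, or think the change repairs the sample size. It does not: at the protocol's own sizes the result is still below 80%.

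**The gain depends on which pairs are tested.** It applies to A-B and A-C. The Sample size calculation names A-B and B-C, and with B and C both assumed to reach 45% there is no B-C difference to detect. This stands, and the pairs have to be reconciled in the same edit.

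**Networks are ignored.** The 14 networks are the units of randomisation, but the calculation, like the protocol's own, allows for no network-level variation. The absolute power figures are conditional on that.

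**Conclusion.** The point holds as a cheap improvement. When B, C and A have all been rejected, a Holm step in stage three rejects everything the fixed split rejects and sometimes more, and family-wise error stays at or below 5%. The probability of rejecting both contrasts rises by about 10 points at the protocol's own sizes and by about 7 points if the stated 80% is accepted. These figures rest on the 2:1:1 allocation, a design effect of 8.415 with two cases per patient, no network-level variation, and A-B and A-C as the pairs.

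The calculation also shows that the stated sample size matches 80% power for a single contrast at 2.5%, which leaves about 67% for both. The case for using the idle level is stronger for that reason, although Holm does not close the whole gap.

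**What to change.** Add to the third stage in the Outcome evaluation section:

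> If both A-B and A-C are open, they are tested by Holm: the smaller p-value at 2.5% and, if rejected, the other at 5%. If only one is open, it is tested at 2.5%.

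The last clause is needed: when only one of B and C was rejected in stage one, only 2.5% has been carried forward.

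In the same edit, change the third-stage pairs in the Sample size calculation from A-B and B-C to A-B and A-C, so that both sections cover the same hypotheses. State how confidence intervals for the two contrasts will be reported.

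The cost is a few sentences, written before the final analysis. No additional data or patients are needed.

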### Randomisation procedure

The allocation to the three arms of the study is done by the study statisticians, using a computer program, and concealed from all others in the project. The 14 practice networks are allocated to one of the three intervention arms under the constraints that the arms contain a similar number of practices (not more than one practice difference) based on an estimated participation rate of practices within the networks and that intervention arm A contains 4 practice networks and intervention arms B and C each 5 practice networks. From a total of 34,650 possible allocation outcomes, 112 meet this requirement, from which a computer program randomly picks one.

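### Whole networks are randomised, but the confirmatory model and sample size stop at the practice, so the between-arm tests do not assure the stated 5% level if networks differ

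*Protocol article*

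**What the plan says.** **Allocation.** Under Randomisation procedure: "The 14 practice networks are allocated to one of the three intervention arms". The constraint is that "intervention arm A contains 4 practice networks and intervention arms B and C each 5 practice networks". The network is the unit of randomisation.

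**Analysis.** Under Data analysis, Outcome evaluation, one logistic mixed model serves all three stages. Its random part is "A random intercept will be included for patients and for practices". The first two stages test before against after within an arm. For the between-arm stage, "For the comparisons in the third stage, the intervention group will be included as fixed effect additionally". A global level of 5% is claimed, with 2.5% for each local between-arm test. No network term, network-level analysis or network-based degrees of freedom is named.

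**Sample size.** Under Sample size calculation, "an intra-cluster correlation coefficient (ICC) for patients in practices of 0.05 and of 0.7 for cases clustered in patients is assumed". No network ICC is given there or elsewhere.

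**Related statements.** The Background expects social influence and spread of practice within networks. The comparison with standard care is to use 14 virtual clusters, so the network level is recognised there. The Discussion concedes that the number of allocated units is small, but the model is unchanged by this.

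**The concern.** In a cluster randomised trial, the precision of a between-arm comparison is limited by the number of randomised clusters. A–B compares 4 networks with 5, which leaves 4 + 5 − 2 = 7 degrees of freedom. With practice as the highest random level, the model takes its information from about 64 practices per arm (193 / 3). If practices in one network resemble each other more than practices in different networks, the standard error is too small and the confidence interval too narrow. Such resemblance is plausible on the protocol's own account: quality circles and local multidisciplinary groups are part of the programmes, and contagion within networks is a subject of the process evaluation.

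At stake are the confirmatory comparisons between programmes, and the 80% global power, which was computed without the network level.

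**Working it through.** **1. The plan's own sample size.** Two-sided chi-squared test of 50% (A) against 45% (B), alpha 0.025, power 80%, allocation 2:1, no continuity correction: 2,844.01 patients in A and 1,422 in B.
- Design effect: (1 + 79 × 0.05) × (1 + 0.7) = 4.95 × 1.7 = 8.415.
- A: 2,844.01 × 8.415 = 23,932.4 (stated 23,933).
- B: 1,422 × 8.415 = 11,966.1 (stated 11,967).

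The stated figures reproduce after rounding up, with no network factor.

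**2. Standard error of A–B.** From the protocol: 193 practices, practice ICC 0.05, and 23,934 / 193 = 124 patients per practice per year. Assumed: equal network sizes (A 4 × 16 = 64 practices, B 5 × 13 = 65), variance 0.25, and a network ICC ρ added to the practice ICC.
- Without networks: 0.25 × (0.05/64 + 0.95/(64 × 124)) + 0.25 × (0.05/65 + 0.95/(65 × 124)) = 0.000447; SE 0.0211.
- Network term: 0.25 × ρ × (1/4 + 1/5) = 0.1125ρ.
- At ρ = 0.005 the term is 0.00056, already more than everything in the planned model; SE about 0.032.
- At ρ = 0.01 the term is 0.00113; SE about 0.040.

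**3. True error of the A–B test at nominal 2.5%.** Simulation under the null, 20,000 trials per setting, normal approximation on practice means. The planned structure is represented by a t test on practice means, so that the practice variance absorbs part of the network variance, as a fitted practice intercept would. Patients per practice: 124, or 320 (4 quarters × 80).

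| Assumed network ICC | Practice-level test |
|---|---|
| 0 | about 2.5% |
| 0.001 | about 4% |
| 0.002 | 6–7% |
| 0.005 | 12–13% |
| 0.01 | 20–21% |
| 0.02 | 30–32% |

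A t test on network means (7 df) stayed at 2.2–2.7% throughout. Counting A–B and A–C together, with the 1.7 patient factor omitted or included making little difference, at least one false finding occurs in about 20% of trials at ICC 0.005 and 31% at 0.01.

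**4. Does the hierarchy protect?** Hardly. On the stated rates and sample size, each before/after test has power above 99.9%, so the third stage is almost always reached.

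**5. Before/after tests.** A stable network effect cancels within an arm: simulated error stays at 2.4–2.5% even at network ICC 0.05. Variation in change does not cancel. With 64 practices, 124 patients each, variance 0.24 (0.61 × 0.39) and an assumed between-period practice correlation r:
- Modelled variance: 2 × 0.95 × 0.24 / (64 × 124) = 0.0000575; SE 0.00758.
- Omitted variance: 2 × 0.05 × 0.24 × (1 − r) / 64 = 0.0000375 (r = 0.9) or 0.0000750 (r = 0.8); true SE 0.00974 or 0.01151.
- Error: 2 × (1 − Φ(2.2414 × modelled SE / true SE)) = 8.1% (r = 0.9) or 14.0% (r = 0.8).

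**6. Power of a valid A–B test.** Non-central t, 7 df, critical value 2.841, difference 0.05. At network ICC 0, power is 35% (124 patients, variance within practices inflated by 1.7) to 42% (320 patients, no inflation). At 0.01 it is about 12% in all these settings.

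**The case against.** **No network ICC is given.** This stands. A reader might infer that the false-positive rate of the primary analysis is far above 5%. The documents do not support that as a fact: at network ICC 0 the planned test holds its level. The size is conditional and can only be shown as a range.

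**Not every stage is affected in the same way.** This also stands. A missing network intercept does no harm to the before/after tests. If the third stage were a test of group-by-time interaction, a stable network effect would cancel there too, and network-by-period variance would matter instead. However, the analysis section names only a group effect, and the sample size section speaks of rates after the intervention.

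**Larger before/after errors can be computed.** With 320 patients per practice, step 5 gives about 17% and 28%. That pairing means 64 × 320 = 20,480 patients per arm, or 61,440 over three arms, against a planned total of 47,867. The correlations of 0.9 and 0.8 are themselves assumptions.

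**A–B and A–C are not the only randomised contrasts.** Correct: B–C is randomised as well, and the sample size section lists it where the analysis section lists A–C.

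**The SAP may add the network level, and the small number of networks is disclosed.** This does not answer the point. The article does not leave the random effects open; it names them, and they stop below the unit of randomisation. The disclosure changes neither the model nor the power.

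**Conclusion.** The point holds for the third-stage tests, conditional on network variance. As stated, the model does not assure the 5% level for A–B and A–C. The true error of A–B at nominal 2.5% runs from about 2.5% (network ICC 0) to 30–32% (0.02), and is 12–13% at 0.005, one tenth of the assumed practice ICC. These figures rest on assumed network ICCs, equal network sizes and a normal approximation; the constraint on the randomisation was not modelled.

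For the before/after tests the risk is a separate one, omitted practice-by-period and network-by-period variation. The documents do not allow its size to be fixed; 8% and 14% are illustrations. Inflation of the whole testing hierarchy by the missing network intercept is not shown.

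The 80% global power is unsupported once the network level is counted. Because the between-arm tests are the confirmatory comparison of the programmes, this should be corrected before the analysis.

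**What to change.** - **Third stage:** include the network as a random effect, with network-by-period variation if the contrast is one of change, and use network-based small-sample degrees of freedom (about 7 for A–B). Alternatively, analyse network-level summaries.
- **First and second stages:** allow for practice-by-period and network-by-period variation. A network intercept alone would not cure these tests.
- **Power:** restate the 80% with the network level included, over a stated range of network ICCs.
- **Permutation test:** use one only if the admissible allocations are first regenerated. The stated total of 34,650 equals 12!/(4! 4! 4!), that is 12 networks split 4/4/4; 14 networks split 4/5/5 give 14!/(4! 5! 5!) = 252,252. The set available for each contrast must also be shown to be large enough: reaching 2.5% needs at least 1/0.025 = 40 equally likely allocations.

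**Cost.** No new data are needed, only changes to the model and to the power statement. The price is wider confidence intervals and a much less favourable power. Variance components will also be poorly estimated from 4 or 5 networks per arm, which favours the simpler network-level summaries.
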